### Data monitoring body

2.9

Data is monitored centrally by members of the central coordinating center. Members occasionally visit collaborating hospitals to review source materials according to an order from the steering committee. Responsible authorities, related ethics committees, and directors of collaborating hospitals have the right to review the source material if necessary.

### Data and safety monitoring board

2.10

An independent data and safety monitoring board (DSMB) oversees the conduct of the trial. Any unexpected event is immediately reported to the DSMB. All safety endpoints are analyzed after the inclusion of 100 and 400 patients. In any case of concern regarding the safety of the participants, the steering committee recommend continuing, stopping, or modifying the trial.

### Statistical analyses

2.11

An intention-to-treat (ITT) analysis will be applied according to the consolidated standards of Reporting Trials (14). As needed, an analysis will be performed on the per-protocol set as a sensitivity analysis of the ITT results. Patient demographic data will be analyzed descriptively. Categorical variables will be assessed using the chi-square test or Fisher’s exact test. In contrast, continuous variables will be assessed using Student’s *t*-test or Wilcoxon rank-sum test, as appropriate. The primary outcome is the proportion of patients with one or more complications at 7 days between the rapid EN and conventional EN groups, as analyzed using univariate logistic regression analysis. Multivariate logistic regression analysis adjusted for potential confounders was performed as a sensitivity analysis. The primary outcome’s odds ratio (OR) will be calculated with the corresponding 95% confidence interval (CI). This clinical trial aimed to demonstrate the non-inferiority of Rapid EN over Conventional EN. If noninferiority is statistically demonstrated for the primary endpoint and the incidence in the rapid EN group is lower than that in the conventional EN group, superiority tests will be implemented. All statistical tests are one-sided, and *p* < 0.025 are considered statistically significant.

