### Randomization

2.3

Eligible patients are randomized into a 1:1 ratio using a web-based data management system to undergo either rapid administration (rapid EN group) or conventional administration (conventional EN group) of EN within 72 h of admission. Using a minimization algorithm, we balanced the number of patients in the two treatment groups at each hospital.

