### Treatment or intervention

2.4

All the patients received EN using dobhoff tube, NG tube or PEG tube. The enteral feeding dose was 100 mL for the first 3 days and was determined by each institution for each patient for 4–7 days. EN was administered at a rate of 100 mL in 5 min for 7 days in patients randomized to the Rapid EN group and 100 mL in more than 30 min in patients randomized to the Conventional EN group. The type of enteral nutritional supplement is unspecified and freely chosen by each patient.

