### Sample size estimates

2.8

A previous observational study (9) showed that the proportion of patients with one or more complications, defined as vomiting, diarrhea, or pneumonia, was 22/45 (48.9%) in the rapid EN group and 14/26 (53.8%) in the conventional EN group. Based on previous reports, the non-inferiority margin was defined as a minimum clinically important difference (MCID) of 5% in the outcome (13). According to those results, we estimated that 622 patients would need to be enrolled to detect non-inferiority of the rapid EN group compared with the conventional EN group, based on a 1-sided α level of 0.025 and a power of 0.80. In total, 700 patients (350 per intervention and control group) were recruited, accounting for possible treatment failures, protocol violations, and dropouts.

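### Allocation is balanced by hospital but the primary model ignores hospital, so the primary interval is somewhat too wide if complication rates differ between hospitals

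*Protocol article*

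**What the plan says.** Allocation (protocol article, section 2.3): "Eligible patients are randomized into a 1:1 ratio using a web-based data management system", and "Using a minimization algorithm, we balanced the number of patients in the two treatment groups at each hospital". Hospital is the only balancing factor named.

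Analysis (section 2.11): the proportion with at least one complication at 7 days is compared between arms, "as analyzed using univariate logistic regression analysis". The effect measure is an odds ratio with a 95% confidence interval. Adjustment appears once: "Multivariate logistic regression analysis adjusted for potential confounders was performed as a sensitivity analysis". The covariates are not listed, and hospital is not mentioned in any model.

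Source of hospital differences (section 2.4): the feeding volume is fixed for the first 3 days and after that "was determined by each institution for each patient for 4–7 days".

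Planning figures (section 2.8): the complication rate "was 22/45 (48.9%) in the rapid EN group" and "14/26 (53.8%) in the conventional EN group", a margin of 5%, one-sided alpha 0.025, power 0.80, 622 patients required and 700 targeted.

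**The concern.** Balancing the arms within hospitals means that a hospital with a high complication rate adds about equally to both arms. Differences between hospitals therefore cancel from the treatment comparison. A treatment-only model does not know this: it estimates its standard error as if allocation had ignored hospital, so between-hospital variation stays in. The reported interval is wider than the real sampling variation of the estimate.

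In a non-inferiority trial the upper limit has to fall below the margin, so an interval that is too wide costs power. The plan has little to spare (see the first step of the check). Hospital differences are plausible because the volume on days 4 to 7 is set by each institution.

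**Working it through.** **Inputs.** Rates 48.9% (22/45) and 53.8% (14/26), margin 5% read as percentage points, one-sided alpha 0.025, N = 700, 1:1 (section 2.8). The ICC and the number of hospitals are not in the documents and are assumed.

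**1. The plan's sample size, for the base power.** n per arm = [pC(1−pC) + pT(1−pT)] (z_α + z_β)² / (margin + pC − pT)². With exact fractions the variance sum is 0.2485 + 0.2499 = 0.4984 and the distance to the margin is 0.05 + 0.0496 = 0.0996.
- One-sided 0.025: 0.4984 × 7.849 / 0.009915 gives 395 per arm, N = 790.
- One-sided 0.05: 0.4984 × 6.183 / 0.009915 gives 311 per arm, N = 622.

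The stated 622 therefore reproduces at one-sided 0.05, not at the stated 0.025. At 0.025 with 700 patients and the rounded rates, SE = √(0.4984/350) = 0.0377 and d = 0.05 + 0.049 = 0.099. Power is Φ(0.099/0.0377 − 1.96) = Φ(0.663), about 75%. If both true rates are 53.8%, it is about 26%.

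**2. Effect of leaving hospital out (risk-difference scale).** Under hospital-balanced allocation the true SE is about f = √(1 − ICC) times the unadjusted SE. Then:
- excess width of the unadjusted interval = 1/f − 1
- its actual one-sided type I error = 1 − Φ(1.96/f)
- power, unadjusted = Φ((d − 1.96 SE)/(f SE))
- power, hospital-adjusted = Φ(d/(f SE) − 1.96)

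| ICC (assumed) | f | Too wide by | Type I error, unadjusted | Power, unadjusted | Power, adjusted | Gain (points) |
|---|---|---|---|---|---|---|
| 0 | 1.000 | 0% | 2.50% | 74.6% | 74.6% | 0 |
| 0.02 | 0.990 | 1.0% | 2.39% | 74.9% | 75.5% | 0.6 |
| 0.05 | 0.975 | 2.6% | 2.22% | 75.2% | 76.8% | 1.6 |
| 0.10 | 0.949 | 5.4% | 1.94% | 75.8% | 79.0% | 3.2 |

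**3. What these ICCs mean.** The SD of hospital rates is √(ICC × 0.538 × 0.462): 7.1, 11.1 and 15.8 points for ICC 0.02, 0.05 and 0.10. Taking 53.8% ± 1.96 SD, about 95% of hospitals lie at 40–68%, 32–76% and 23–85%. ICC 0.10 is already a wide spread.

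**4. Simulation.** With 700 patients, 10 equal balanced hospitals and 1,500 runs, power without and with hospital was 76.5% and 76.6% (ICC 0.02), 73.4% and 74.8% (ICC 0.05), and 76.8% and 79.4% (ICC 0.10). The Monte Carlo error of each level is about √(0.75 × 0.25/1500) = 1.1 points; both analyses use the same simulated trials. A larger simulation (10 or 14 equal hospitals, 20,000 runs) gave 75.3% to 75.8% at a between-hospital log-odds SD of 0.3, and about 75.6% to 77.6% at SD 0.5. By p(1−p)σ² these SDs are ICCs of 0.2486 × 0.09 = 0.02 and 0.2486 × 0.25 = 0.06. Both simulations agree with the table in direction and approximate size.

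**5. The planned odds-ratio scale.** The 5-point margin at 53.8% is an odds ratio of (0.588/0.412)/(0.538/0.462) = 1.226, log 0.203. At ICC 0.10 the simulated log odds ratio was −0.199 (SE 0.1522) without hospital and −0.217 (SE 0.1592) with hospital terms. The distance to that fixed margin in SEs is (0.203 + 0.199)/0.1522 = 2.64 and (0.203 + 0.217)/0.1592 = 2.64. Power was 76.7% and 76.6%. The conditional estimate moves away from 1 and its SE grows in step, so nothing is gained.

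**The case against.** The strongest reply is that this costs only efficiency. The error is conservative: in a safety non-inferiority trial it makes a false claim of non-inferiority less likely, not more. That stands. A reader might infer that omitting the allocation factor invalidates the test or inflates type I error; the working shows the opposite.

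The size also rests wholly on assumption. A reader might infer gains of 5 points or more. In the larger simulation, power rose from about 77% to 83% only at a log-odds SD of 1.0. That puts the middle 95% of hospitals at roughly 14% to 89% around 53.8%, and nothing in the documents supports such a spread. Choice of formula cannot be used to argue for large hospital differences either, because section 2.4 leaves it to each patient, not to the hospital.

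Two further limits stand. The list of potential confounders is of the kind normally left to the analysis plan, so it cannot be said that hospital is barred from the sensitivity model. The primary model is different: the article itself fixes it as univariate, and adding hospital to a sensitivity analysis would not change it. Also, the gain requires moving from the odds ratio to a risk difference, so it is not just a matter of adding a covariate.

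Finally, the power shortfall in section 2.8 (622 stated, about 790 needed at one-sided 0.025) is a separate and much larger problem. A reader might infer that adjusting for hospital repairs it. It does not: at ICC 0.10, power reaches 79.0%, and at smaller ICCs it stays nearer 75%.

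**Conclusion.** The point holds as a modest loss of efficiency. The plan balances on hospital and then analyses as if it had not. If hospital rates differ, the primary interval is somewhat too wide and the test conservative. For ICC 0.02 to 0.10, the loss is about 1% to 5% of interval width and about 0.5 to 3 points of power at 700 patients, with one-sided type I error of about 2.4% to 1.9% instead of 2.5%. At ICC 0 there is no loss.

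The direction is certain whenever hospital rates differ. The size is not, because it depends on an ICC that the documents do not give. It also assumes roughly equal hospitals, close balance within each, a margin in percentage points and the planned rates. The change is worth making because the allocation factor is already recorded and the trial has no power to spare.

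**What to change.** Make the primary analysis one of these:
- a hospital-stratified risk difference with Mantel-Haenszel weights and its 95% confidence interval; or
- a logistic model with treatment and hospital, standardised to a marginal risk difference, with the standard error taken from the adjusted model.

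Conclude non-inferiority if the upper 95% limit is below 5 percentage points. Keep the unadjusted analysis as a sensitivity analysis. Do not simply add hospital to the logistic model and report the conditional odds ratio.

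The cost is small. No new data are needed, since hospital is known from allocation. A rule for pooling small hospitals must be written in advance, because a hospital with patients in only one arm contributes nothing to a stratified estimate. Section 2.1 gives conduct as October 2020 to March 2024, so the change may come late. It must be fixed and dated before unblinded data are seen, by people who have not seen comparisons by arm.

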### Participants

2.2

Patients aged ≥20 years who developed stroke within 7 days from onset, had difficulty with oral intake and could raise their head more than 30 degrees represented the target population in the Rapid EN trial. Patients who had difficulty with oral intake were defined as having severely altered consciousness (JCS 10–300), or modified water swallowing test (MWST) (10) <4. Patients with obstructive gastrointestinal tract disease unfit for enteral feeding were excluded. Table 1 shows the inclusion and exclusion criteria.

**Table 1 tab1:** Inclusion and exclusion criteria.

Inclusion criteria
∙Age ≥ 18 years at the time of giving informed consent. ∙Clinical diagnosis of acute ischemic stroke within 7 days from onset. ∙Patients who can be randomized within 72 h from admission. ∙Patients who have difficulty with oral intake are defined as severely altered consciousness (JCS 10–300) or modified water swallowing test <4. ∙Patients who can raise their head more than 30 degrees. ∙Written informed consent by the patient or next of kin.
Exclusion criteria
∙Obstructive diseases of the gastrointestinal tract. ∙Pregnancy or possibility of pregnancy. ∙patients with an expected life expectancy of 90 days or less. ∙Patients who are deemed by the investigator or sub-investigator to be unsuitable for participation in this study.

JCS, Japan Coma Scale.

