### Clinical assessments

2.5

Performances at baseline, three complications of enteral nutrition, including vomiting, diarrhea, and pneumonia, for 3–7 days from the start of EN, location of stroke, the length of hospital stay and clinical outcomes will be assessed by a third independent observer blinded to the group assignment. Vomiting was defined as one or more episodes associated with EN initiation. Diarrhea was defined as a score of 6 or 7 on the Bristol Stool Scale (11), persisting for more than 2 days. Pneumonia was defined as physician-observed pneumonia based on imaging and clinical status. Clinical outcomes were assessed using the modified Rankin scale (mRS) score (range, 0 [no symptoms] to 6 [death]) (12); favorable clinical outcomes were defined as an mRS score of 0–2 at 90 days after stroke onset.

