### Secondary outcomes

2.7

Secondary outcomes were total time spent on EN, incidence of vomiting, diarrhea, and pneumonia within 3 and 7 days of EN, incidence of one or more of the three complications in patients with ischemic or hemorrhagic stroke, and rate of favorable clinical outcome. The efficacy and safety endpoints are presented in Table 2.

**Table 2 tab2:** Primary and secondary outcomes.

Primary outcome
∙Incidence of vomiting or diarrhea or pneumonia within 7 days of initiation of enteral nutrition (non-inferiority).
Secondary outcomes
∙Total time spent on enteral nutrition within 7 days of initiation of enteral nutrition (hours).
∙Incidence of vomiting within 7 days of initiation of enteral nutrition.
∙Incidence of diarrhea within 7 days of initiation of enteral nutrition.
∙Incidence of pneumonia within 7 days of initiation of enteral nutrition.
∙Incidence of vomiting or diarrhea or pneumonia within 3 days of initiation of enteral nutrition (non-inferiority).
∙Incidence of vomiting within 3 days of initiation of enteral nutrition.
∙Incidence of diarrhea within 3 days of initiation of enteral nutrition.
∙Incidence of pneumonia within 3 days of initiation of enteral nutrition.
∙Incidence of vomiting or diarrhea or pneumonia within 7 days of initiation of enteral nutrition in ischemic stroke patients (non-inferiority).
∙Incidence of vomiting or diarrhea or pneumonia within 7 days of initiation of enteral nutrition in intracerebral hemorrhage and subarachnoid hemorrhage patients (non-inferiority).
∙Favorable outcome defined as mRS score 0–2 at 90 days after stroke onset.

mRS, modified Rankin Scale.

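### The unadjusted primary model is valid, but a prespecified standardised risk difference adjusted for entry severity would cheaply recover some precision

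*Protocol article*

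**What the plan says.** Section 2.11 (Statistical analyses) compares the proportion with one or more complications at 7 days "as analyzed using univariate logistic regression analysis", and reports an odds ratio with a 95% confidence interval. On adjustment it says: "Multivariate logistic regression analysis adjusted for potential confounders was performed as a sensitivity analysis".

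The baseline information comes from elsewhere in the protocol article:

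- **Severity.** Section 2.2 (Participants): "Patients who had difficulty with oral intake were defined as having severely altered consciousness (JCS 10–300), or modified water swallowing test (MWST) (10) <4".
- **Baseline assessment.** Section 2.5 opens its list with "Performances at baseline, three complications of enteral nutrition", but does not say what baseline performance consists of.
- **Stroke type.** Section 2.7 lists as a secondary outcome the "incidence of one or more of the three complications in patients with ischemic or hemorrhagic stroke", whereas Table 1 admits only a "Clinical diagnosis of acute ischemic stroke within 7 days from onset".
- **Balancing.** Section 2.3 names hospital as the only factor balanced by minimisation.

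Section 2.8 sets a 5% margin, one-sided alpha 0.025 and power 0.80, with 622 patients required and 700 recruited.

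**The concern.** Non-inferiority is decided by one confidence limit, so an interval wider than it needs to be lowers the chance of a conclusive answer. Depth of coma and failed swallowing plausibly predict vomiting and pneumonia, two of the three components of the primary outcome. The article's discussion points the same way: it ties dysphagia screening to preventing pneumonia and says that vomiting from brain injury may be hard to tell from vomiting due to feeding. In a randomised comparison the main reason to adjust for such variables is precision. Placing them only in a sensitivity analysis aimed at confounding leaves that precision out of the primary decision. The design does not balance them either, since minimisation uses hospital alone.

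**Working it through.** **Inputs (section 2.8).** Rapid p1 = 22/45 = 0.4889; conventional p0 = 14/26 = 0.5385; margin 5%, read as 5 percentage points; one-sided alpha 0.025; 350 per arm.

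**The plan's own figure.** n per arm = [p1(1−p1) + p0(1−p0)] × (z_alpha + z_power)² / (p0 − p1 + 0.05)².

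- Variance sum: 0.2499 + 0.2485 = 0.4984. Distance to margin: 0.0496 + 0.05 = 0.0996.
- Alpha 0.025: 0.4984 × (1.960 + 0.842)² / 0.0996² gives 395 per arm, 790 in total, not 622.
- Alpha 0.05: 0.4984 × (1.645 + 0.842)² / 0.0996² gives 311 per arm, 622 in total.

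So 622 matches one-sided 0.05 rather than the stated 0.025.

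**Power at 350 per arm, unadjusted.** SE = √(0.4984/350) = 0.0377. Power = Φ(0.0996/0.0377 − 1.96) = Φ(0.68) = 75.1%.

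**Power with adjustment.** For a covariate-adjusted risk difference the variance is multiplied by about (1 − R²), where R² is the share of outcome variance explained by the covariates. The document gives no R², so a range is shown:

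| R² | Power at 700 | Total N for 80% |
|---|---|---|
| 0 | 75.1% | 790 |
| 0.02 | 76.0% | 776 |
| 0.05 | 77.3% | 752 |
| 0.10 | 79.4% | 712 |
| 0.15 | 81.6% | 672 |

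Reaching 80% with 700 patients needs R² of about 0.113.

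**Does the gain depend on the effect measure?** Trials of 700 patients were simulated (4000 per scenario) with a binary severity factor (50% of patients) and a binary stroke-type factor (35% haemorrhagic). These frequencies and the covariate odds ratios are assumptions. The risk difference was tested against 5 points. The odds ratio was tested against 1.226, the odds ratio that takes 53.8% to 58.8%.

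| Covariate ORs (severity / stroke type) | R² | Risk difference: unadjusted → standardised | Odds ratio: unadjusted → adjusted | SE of log OR |
|---|---|---|---|---|
| 1.5 / 1.2 | 0.012 | 74.8 → 76.2% | 74.8 → 76.0% | 0.152 → 0.153 |
| 2 / 1.5 | 0.037 | 73.6 → 76.2% | 73.6 → 74.6% | 0.152 → 0.155 |
| 3 / 1.5 | 0.078 | 74.7 → 78.7% | 74.7 → 75.4% | 0.152 → 0.159 |
| 4 / 2 | 0.126 | 75.3 → 80.8% | 75.3 → 75.9% | 0.152 → 0.163 |

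The standardised risk difference gains 1.4, 2.6, 4.0 and 5.5 points. A separate run of the same scenarios gave 0.7, 1.6, 3.3 and 6.1. The adjusted odds ratio gains only 0.6 to 1.2 points, and its standard error rises. The benefit therefore needs both the covariates and the risk-difference scale.

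**Shift between unadjusted and adjusted odds ratios.** The planning rates give an unadjusted odds ratio of (22/23)/(14/12) = 0.820. In the strongest scenario above the adjusted odds ratio is 0.797, with no confounding. On the log scale the shift is ln(0.820/0.797) = 0.028, about 0.2 of the standard error of 0.152.

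**The case against.** The strongest reply is that nothing here is wrong: an unadjusted comparison of randomised arms is valid, and section 2.11 already plans an adjusted analysis. That stands, and it limits the point to efficiency. Other parts of the reply also stand:

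- **The covariate list.** A reader might fault the article for not naming the covariates. Such a list is commonly left to the analysis plan, which is not shown, so its absence is not a finding. That adjustment is not primary is different, because section 2.11 states it.
- **Prognostic strength.** It may be modest. The composite includes diarrhoea, which the article says can be secondary to infection. The covariates are themselves entry criteria, so their range is restricted. They also overlap, since a patient who does not meet the consciousness criterion must meet the swallowing one.
- **Availability.** The entry rule joins the two tests with an or, so not every patient need have both. Stroke type is a constant if Table 1 is taken literally.
- **Cost.** A reader might infer that the precision is free. It requires changing the effect measure as well as the model, and a late change could look post hoc: section 2.1 dates the trial October 2020 to March 2024, and section 2.10 has safety analyses after 100 and 400 patients.

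A reader might also infer that the adjusted and unadjusted odds ratios cannot be compared at all, because they differ even under perfect balance. The shift is real but small against the standard error, so it is a minor caution.

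These replies do not remove the core: the entry severity measure is collected, and using it in the primary analysis on a risk-difference scale would usually narrow the interval.

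**Conclusion.** The point holds as a cheap improvement of low severity. The primary analysis leaves unused a baseline measure that is already collected, in a trial with about 75% power at 350 per arm on its own inputs. The likely gain is about 1 to 6 points of power. It approaches zero if the covariates are weak, and exceeds 5 points only in the strongest simulated scenario.

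This rests on the margin being 5 percentage points, on the planning rates being true, and on assumed covariate strengths and frequencies. If only ischaemic stroke is enrolled, the part of the gain due to stroke type disappears.

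One tempting reading is that the univariate model causes the shortfall from 80%. The document does not support that: the shortfall comes from the sample size, since 622 matches one-sided alpha 0.05 and the stated 0.025 needs 790. Nor would adjustment rescue the trial if the arms truly do not differ: at 53.8% in both, power at 700 is about 26% unadjusted and 28.7% at R² = 0.10.

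**What to change.** In section 2.11, before anyone choosing the model has seen data by arm:

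1. Make the primary analysis a logistic model with treatment and a short fixed list of entry covariates: JCS category and the MWST criterion, with a category for patients not tested. Add stroke type only if Table 1 and Table 2 are reconciled so that more than one type is enrolled.
2. From that model report the standardised (g-computation) difference in the proportion with one or more complications, with a two-sided 95% confidence interval, and judge non-inferiority by comparing its upper limit with the 5-point margin. This also puts the decision on the scale on which the margin was set.
3. Keep the unadjusted risk difference as the sensitivity analysis, so that both results are on one scale.

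The cost is wording, a slightly more complex primary analysis and a rule for untested patients; no new data or patients are needed. If data by arm have already been seen by those choosing the model, keep the planned primary analysis and report the adjusted risk difference as a supplementary result, labelled as added later.

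### The non-inferiority margin is set as a difference in proportions but the primary effect measure is an odds ratio, and no stated rule connects the two

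*Protocol article*

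**What the plan says.** Section 2.8 (Sample size estimates) of the protocol article takes its planning rates from an earlier observational study: the complication proportion "was 22/45 (48.9%) in the rapid EN group" and "14/26 (53.8%) in the conventional EN group". It then states that "the non-inferiority margin was defined as a minimum clinically important difference (MCID) of 5% in the outcome". The size follows: "we estimated that 622 patients would need to be enrolled to detect non-inferiority", "based on a 1-sided α level of 0.025 and a power of 0.80". This is raised to 700, or 350 per arm.

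Section 2.11 (Statistical analyses) describes the primary outcome as a proportion compared between arms, "as analyzed using univariate logistic regression analysis", and adds that the "odds ratio (OR) will be calculated with the corresponding 95% confidence interval (CI"). A multivariable logistic model is the sensitivity analysis. All tests are one-sided at p < 0.025. Superiority is tested only after non-inferiority has been shown and if the observed incidence is lower in the rapid arm.

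The article gives no odds-ratio margin, no risk difference with a confidence interval, no conversion from the model to a risk difference, and no statement of which confidence limit is compared with what.

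**The concern.** A non-inferiority verdict comes from comparing a confidence limit with a margin, so both must be on one scale. Here the margin is a difference in proportions and the interval is for an odds ratio. The odds ratio that corresponds to 5 points depends on the control rate, so no single odds-ratio limit stands for the margin at every rate. Non-inferiority on this outcome is the trial's aim and the gate to superiority testing, in an open-label trial. If the link between margin and interval is not fixed in advance, the verdict is open to a choice made after the event rates are known.

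**Working it through.** **Inputs.** From section 2.8: control rate pC = 14/26 = 0.5385; rapid rate pR = 22/45 = 0.4889; margin 5%; one-sided α 0.025; power 0.80; 622 patients needed; 350 per arm planned. Allocation is 1:1 (section 2.3). Control rates other than 53.8% are assumptions, because the article gives no other control rate.

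**1. Which scale is the margin on?** The word absolute is not printed, so I tried to reproduce 622. For a risk difference with unpooled variance:

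n per arm = (z₁₋α + z₀.₈₀)² × [pC(1−pC) + pR(1−pR)] / (0.05 + pC − pR)²

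The variance term is 0.2485 + 0.2499 = 0.4984, and the distance to the margin is 0.05 + 0.0496 = 0.0996.

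- One-sided 0.05: 6.183 × 0.4984 / 0.0996² = 310.8, so 311 per arm and **622** in total, an exact match.
- One-sided 0.025, as stated: 7.849 × 0.4984 / 0.0996² = 394.6, so 395 per arm and **790** in total.

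(Both results use unrounded inputs.) A margin of 5% relative to the control rate gives 1054 at one-sided 0.05 and 1338 at 0.025. So 622 supports an absolute 5-point margin, but only at an α that the article does not state. The gap between 622 and 790 is a separate error. It does not change the scale of the margin.

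**2. The odds ratio equal to +5 points.** OR = [(p + 0.05)/(0.95 − p)] / [p/(1 − p)] for control rate p. The last column is the excess allowed by a limit fixed at the planning-rate value, 1.226 (1.23 when rounded).

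| Control rate | OR equal to +5 points | Points allowed by the fixed limit |
|---|---|---|
| 60% (assumed) | 1.24 | 4.8 |
| 53.8% (planning) | 1.23 | 5.0 |
| 50% (assumed) | 1.22 | 5.1 |
| 40% (assumed) | 1.23 | 5.0 |
| 35% (assumed) | 1.24 | 4.8 |
| 30% (assumed) | 1.26 | 4.4 |
| 20% (assumed) | 1.33 | 3.5 |
| 10% (assumed) | 1.59 | 2.0 |

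**3. Can the verdicts differ?** Take hypothetical results of 35/350 (rapid) against 40/350 (conventional). The risk difference is −1.4 points with standard error 2.34 points, so the upper limit is −1.43 + 1.96 × 2.34 = +3.2 points: non-inferior at 5 points. The odds ratio is 0.861 with log standard error 0.245, so the upper limit is exp(−0.150 + 1.96 × 0.245) = 1.39, which fails a limit of 1.23. This example needs rates near 10%.

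**4. Power at the planning rates, 350 per arm, one-sided 0.025.** The standard error of the difference is √(0.4984/350) = 0.0377.

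- Risk difference against +5 points: Φ(0.0996/0.0377 − 1.96) = Φ(0.68) = 75%.
- Odds ratio against a limit of 1.226: 76%.
- Ordinary test of no difference (OR = 1): Φ(0.0496/0.0377 − 1.96) = Φ(−0.65) = 26%.

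**The case against.** The strongest reply is that the two scales hardly differ where the trial was planned. Between control rates of 35% and 60% a fixed limit of 1.226 allows 4.8 to 5.1 points, and at the planning rates power is 75% on one scale and 76% on the other. The only control rate in the article lies in that range, and nothing in the article predicts 10% or 20%. That stands, and it limits the practical size of the point. It does not remove it: the planning rate rests on 26 patients, so a different rate in the trial is possible.

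A second reply is that a condensed article may leave the decision rule to a statistical analysis plan that is not shown, and that a two-arm logistic model reproduces both observed proportions, so a risk difference follows from it directly. An odds-ratio margin could equally have been fixed in advance. This also stands in part: it would be wrong to say that logistic regression cannot test the margin, or that a margin will be picked after the data are seen. But the article does more than omit a detail. It names an effect measure on a different scale from its own margin, so an analysis plan would have to depart from the published text or supply a margin that the article never gives.

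A reader might also infer that the logistic p-value against OR = 1 will decide non-inferiority, so that the plan tests the wrong hypothesis with 26% power. The article does not say so. It treats showing non-inferiority and testing superiority as separate steps, which argues against that reading. The 26% is what would follow if the default p-value were used by mistake.

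**Conclusion.** The point holds as a mismatch of scale: the margin is a difference in proportions, the stated primary effect measure is an odds ratio, and the article has no rule that joins them. That the margin means 5 percentage points is an inference, supported by its place beside two proportions and by the exact match to 622 at one-sided 0.05.

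The size depends on the control rate. Near 53.8% the choice of scale makes almost no difference. At an assumed 20% or 10%, an odds-ratio limit of 1.23 would be stricter than the stated margin (about 3.5 or 2.0 points in place of 5), and the verdict could turn on the scale. The drop in power from 75% to 26% applies only if the test of OR = 1 were used for non-inferiority, which the text does not state.

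**What to change.** In section 2.11, state that the primary analysis is the risk difference (rapid minus conventional) with a two-sided 95% confidence interval, for example Miettinen–Nurminen, and that non-inferiority is declared if the upper limit is below +5.0 percentage points. In section 2.8, write the margin as 5 percentage points, absolute. Report the odds ratio as supportive. Express the adjusted sensitivity analysis as a standardised (marginal) risk difference from the logistic model, set against the same +5 points.

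An odds-ratio margin that is justified in advance, with the sample size redone on that scale, would also remove the mismatch, but it means more work and moves away from the margin already published.

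The cost is one paragraph, repeated in the analysis plan, and no new data. The change should be documented before any unblinded comparison. If the analysis has already been done, the risk difference should be reported against 5 points and the change of scale disclosed. The gap between 622 and 790 needs its own correction.
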